## Background

Gastric cancer is a common and lethal malignant disease worldwide. Although mortality has decreased substantially, approximately 0.5 million patients die of gastric cancer in China annually [1, 2]. Early diagnosis of gastric cancer and radical gastrectomy improves the prognosis. However, patients have the possibility of rapid or delayed gastric emptying after distal gastrectomy, which impacts their nutritional status and quality of life (QoL) [3, 4]. Specifically, 5–30% of patients develop delayed gastric emptying (DGE) following gastrectomy [5–7]. Postsurgical gastroparesis syndrome (PGS) is also used for this complication [8]. Tomita et al. found that epigastric fullness occurred in 60% of patients who had received pylorus-preserving distal gastrectomy 5 years ago, gastric stasis in the remnant stomach occurred in 40% of these patients, and the gastric emptying function of a liquid and semisolid diet was decreased [9]. Kim et al. showed that over half of postoperative gastric cancer patients had DGE with frequently observed gastric stasis and reflux esophagitis [10]. Jung et al. reported that the incidence of food retention was 55.5%, 31.9%, and 20.9% at 3, 12, and 24 months, respectively, after distal gastrectomy for early gastric cancer patients [11].

Nutritional support, glycemic control, prokinetics, antiemetic medications, endoscopic self-expandable stent placement, and surgical intervention in severe cases are considered to be helpful for DGE patients [12]. Nevertheless, prokinetics lack clinical evidence with possible severe side effects, and secondary surgery is not a preferred choice for postoperative patients.

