### Randomization

All eligible patients will be randomly assigned to the TEA group or the sham-TEA group by an allocation ratio of 2:1, and the framework of the trial is assumed as superiority (Fig. 2). The randomization process will be achieved by opening sealed envelopes with computer-generated random numbers by the SPSS 22.0 software. The process will be implemented by a researcher who is not involved in the data collection or analysis.

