### Statistical analysis

Sensitivity analysis will be performed to determine the impact of incomplete records on the results. Intent-to-treat analysis of the results will be performed if there is nonadherence or missing data. Only two data statisticians will have access to the final trial dataset, which will only contain coded data, and they will perform statistical analysis using the SPSS version 22.0 software. Student’s *t* test will be performed to assess the difference in the measurements (the residual rates of radioactivity in the stomach at 45, 60, 75, 90, 105, and 120 min) between the TEA group and the sham-TEA group. Paired Student’s *t* test will be used to compare the differences in serum albumin, NE, TNF-α, IL-1β, IL-6, glucose, LF/HF (sympathovagal ratio), and QoL at baseline and 4 weeks after intervention in each group. The *χ*^2^ test will be used for categorical data such as the PG-SGA, HADS, and adverse events. Univariate and multivariate analyses with multiple linear regression will be used to identify independent predictors of outcome measures. The results will be aggregated as median values. *P* values of < 0.05 will be considered as statistically significant.

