## Discussion

DGE occurs after upper gastrointestinal tract surgery, including gastrectomy, pancreatic surgery, and esophagectomy [5, 31–33]. As the prognosis of gastric cancer patients improves, it turns out to be the main concern for patients with DGE after distal gastrectomy. DGE impacts the patients’ nutritional status and QoL. Moreover, persistent DGE results in psychological diseases and even influences the prognosis of gastric cancer. However, the current treatments of DGE seem unsatisfactory or need invasive interventions, and prokinetics should be used cautiously due to their limited long-term efficacy and significant side effect. EA or TEA has been proven to be an effective treatment for improving gastrointestinal motility in either animal models or clinical cases [17, 23, 24, 34, 35]. Self-administrating TEA has been developed as a more convenient, patient-friendly treatment. It is promising for treating DGE after distal gastrectomy. The purpose of this trial was to evaluate the efficacy of TEA versus sham-TEA in improving gastric emptying function and the safety of TEA. The protocol of this trial is a well-designed, randomized, patient-assessor blinded procedure, which will make the results convincing. Notably, we compared the TEA group versus the sham-TEA group rather than the medical treatment or control group, which ruled out a placebo effect.

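### Eight listed secondary outcomes are tested only within each arm, so no named test compares TEA with sham on them, and 2:1 allocation tilts false patterns towards TEA

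*Protocol article*

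**What the plan says.** All references are to the protocol article. Its Statistical analysis section assigns tests by type of outcome:

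- **Between-arm Student's *t* test:** limited by its parenthesis to "the residual rates of radioactivity in the stomach at 45, 60, 75, 90, 105, and 120 min) between the TEA group and the sham-TEA group".
- **Within-arm paired Student's *t* test:** this "test will be used to compare the differences in serum albumin, NE, TNF-α, IL-1β, IL-6, glucose, LF/HF (sympathovagal ratio"), with the list ending "and QoL at baseline and 4 weeks after intervention in each group".
- **χ² test:** this "test will be used for categorical data such as the PG-SGA, HADS, and adverse events".
- **Regression:** "multiple linear regression will be used to identify independent predictors of outcome measures". Neither the treatment arm nor the outcomes to be modelled are named.

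Under Randomization, "the framework of the trial is assumed as superiority". Elsewhere the article says so when it wants the arms compared: for residual rates, time to 50% residual and total response rates under the primary outcomes, and for the endoscopic findings under the secondary outcomes. It says nothing of the kind for albumin, NE, the cytokines, glucose, LF/HF or QoL.

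**The concern.** A paired test within one arm asks whether that arm changed over 4 weeks. It does not estimate TEA minus sham. Any influence common to both arms, such as placebo response, time since surgery or adjuvant chemotherapy, enters the within-arm change in full, and the sham arm is there to remove it. The Discussion relies on the sham comparison to exclude a placebo effect; for these outcomes the named test does not make that comparison.

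The allocation adds a direction to the problem. At the same true change, a paired test reaches P < 0.05 more often in the larger arm. Under 2:1 allocation the larger arm is always TEA, so equal change in both arms tends to look like an effect of TEA alone. These outcomes carry the nutritional, autonomic, inflammatory and QoL parts of the second study objective.

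**Working it through.** **The plan's own figure.** The article gives none for these outcomes. Its sample size calculation concerns the response rate, and only the arm sizes and loss rate are taken from it.

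**Inputs**
- Arm sizes 60 and 30, with 20% loss (Sample size). This leaves 60 × 0.8 = 48 and 30 × 0.8 = 24.
- P < 0.05 per test (Statistical analysis), taken as two-sided, as in Sample size.
- *d*, the true mean change divided by the SD of change, set equal in both arms so that TEA has no effect. This is an assumption. The article gives no SD or expected change, so a range from 0 to 0.8 is shown.

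**Formulas**
- The paired *t* statistic in an arm of size *n* follows a noncentral *t* distribution with *n* − 1 degrees of freedom and noncentrality *d*√*n*. Power is the probability that its absolute value exceeds the 97.5% point of the central *t* distribution.
- The arms are independent, so P(TEA only) = power in TEA × (1 − power in sham). P(sham only) = power in sham × (1 − power in TEA).

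**Example, *d* = 0.4 at 48/24.** Noncentrality is 0.4 × √48 = 2.77 in TEA and 0.4 × √24 = 1.96 in sham. Power is 0.775 and 0.467. P(TEA only) = 0.775 × (1 − 0.467) = 0.413. P(sham only) = 0.467 × (1 − 0.775) = 0.105.

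**Results (%), per outcome, with no treatment effect**

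| Shared change *d* | Power TEA, n=48 | Power sham, n=24 | TEA only, 48/24 | Sham only, 48/24 | TEA only, 60/30 |
|---|---|---|---|---|---|
| 0 | 5.0 | 5.0 | 4.8 | 4.8 | 4.8 |
| 0.1 | 10.4 | 7.6 | 9.6 | 6.8 | 10.9 |
| 0.2 | 27.4 | 15.6 | 23.1 | 11.3 | 27.0 |
| 0.3 | 53.0 | 29.1 | 37.6 | 13.7 | 40.5 |
| 0.4 | 77.5 | 46.7 | 41.3 | 10.5 | 37.7 |
| 0.5 | 92.4 | 65.0 | 32.3 | 4.9 | 23.8 |
| 0.6 | 98.3 | 80.4 | 19.3 | 1.4 | 11.2 |
| 0.8 | 100.0 | 96.3 | 3.7 | 0.0 | 1.2 |

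With 45 per arm, each one-sided pattern peaks at about 25%. The asymmetry therefore comes from the 2:1 allocation.

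**Check against a between-arm test.** In 40,000 simulated trials at each of *d* = 0, 0.2, 0.3, 0.4 and 0.5, for 60/30 and for 48/24, a two-sample *t* test on change from baseline was falsely significant in 4.8% to 5.2% of trials. The simulated frequencies of *TEA only* agreed with the table.

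**What a between-arm test could detect.** By the normal approximation, the difference in change detectable with 80% power is (1.960 + 0.842) × √(1/60 + 1/30) = 0.63 SD of change at 60/30, and 2.802 × √(1/48 + 1/24) = 0.70 SD at 48/24.

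**The case against.** **These outcomes are secondary.** This stands. The primary residual rates have an explicit between-arm test. The Discussion states the aim narrowly: "The purpose of this trial was to evaluate the efficacy of TEA versus sham-TEA in improving gastric emptying function and the safety of TEA". A reader might infer that the trial's main conclusion is undermined, and the article does not support that. Nor does the problem cover every secondary domain: the endoscopic findings are compared between arms, and the categorical outcomes have a χ² test.

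**The regression might include arm, or an analysis plan that is not shown might add arm contrasts.** Both are possible. But the article presents the regression as a search for predictors and names neither arm nor these outcomes. The paired test is a stated choice, not a detail left open, so the published text still needs correcting.

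**The size depends on an assumed shared change.** This stands, and it is why the whole range is shown. A reader might take the Background figures ("the incidence of food retention was 55.5%, 31.9%, and 20.9% at 3, 12, and 24 months") as proof of natural recovery in these outcomes. They concern food retention, at intervals of many months, and say nothing about albumin, cytokines, LF/HF or QoL over 4 weeks. They make some drift plausible and no more. Regression to the mean is also tempting, but patients are selected on gastric half-emptying time, not on any of these outcomes. It could act only through correlations that the article does not give.

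**A count of false findings.** A reader might multiply the table by 15 measures (seven laboratory and HRV measures plus eight SF-36 scales) and expect about 3 to 6 false *TEA only* results (15 × 0.231 = 3.5; 15 × 0.413 = 6.2). That needs every measure to shift by 0.2 to 0.5 SD in both arms. At 0 or 0.8 SD the same product is 0.7 or 0.6. The article also says only that QoL is tested, not that eight scales are. The count should not be used.

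**Conclusion.** The point holds for the outcomes in the paired-test sentence. As written, the plan names no comparison of TEA with sham for serum albumin, NE, TNF-α, IL-1β, IL-6, glucose, LF/HF or QoL, and the test that it does name cannot support superiority over sham. That conclusion rests on the text alone and holds even if neither arm drifts.

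The size is conditional. If both arms share a true change of 0.2 to 0.5 SD of change, the false pattern *significant in TEA only* arises in about 23% to 41% of cases per outcome at 48/24. It falls to about 5% with no shared change and 4% at 0.8 SD. *Sham only* stays at or below about 14% throughout. It would be too strong to say that the false pattern will often occur; it can occur often if both arms move by a moderate amount.

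This should be corrected, but it is an improvement to secondary analyses and not a threat to the primary comparison.

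**What to change.** For the outcomes in that sentence only, replace the paired *t* tests by a between-arm ANCOVA: 4-week value on treatment arm and baseline value. Report the adjusted TEA minus sham difference with its 95% CI. Where a measure is clearly skewed, analyse baseline and 4-week values on the log scale. Present within-arm changes as description, without P values.

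The cost is a change of wording. The paired test already needs a baseline and a 4-week value from each patient, so no new data or visits are required. The change should be dated and made before unblinding. Readers should be told that at these arm sizes an analysis of change detects only differences of about 0.63 to 0.70 SD of change with 80% power, so a wide interval is not evidence of no effect.

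HADS and PG-SGA are left out of this change. They have a χ² test, and the text gives no assessment times from which to confirm that baseline and 4-week values exist.

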### Outcome measures

#### Primary outcome measures

##### Gastric emptying function

We will evaluate the gastric emptying function of these postoperative patients who visit outpatient clinics. Gastric scintigraphy will help us to evaluate the gastric emptying function and has the advantages of being noninvasive and painless. ^99m^Tc tin colloid will be mixed with a semisolid diet of 200 g of rice gruel with a boiled egg. Radioactive signs will be recorded from diet intake to 120 min afterward, and the residual rates of radioactivity in the stomach at 45, 60, 75, 90, 105, and 120 min will be calculated by a half-life of 9 mTc. We will compare the recorded residual rates and the time to 50% residual rate between the two groups as the primary outcomes.

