##### Total response rates

We will compare the total response rates between the two groups. Meanwhile, we will perform a subgroup analysis by different operation types of Billroth-I, Billroth-II, or Roux-en-Y reconstruction. In fact, some researchers reported that Roux-en-Y reconstruction could destroy the natural small-bowel pacemaker [20–22]. Subgroup analysis of laparoscopic and open surgery will also be included in our results.

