#### Secondary outcome measures

##### Endoscopic features

DGE patients may have chronic inflammation of the upper digestive tract. Thus, endoscopy will be performed to determine reflux esophagitis, gastritis, and gastric stasis in the remnant stomach. We will compare the ratios of reflux esophagitis, gastritis, and gastric stasis between the two groups.

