##### Nutritional status

The change in serum albumin and body mass index (BMI) will be recorded for nutritional status screening and evaluation. Additionally, the scored patient-generated subjective global assessment (PG-SGA) (weight, food intake, symptoms, activities and function, disease state, metabolic demand, and nutritional physical examination) will be used to quickly identify malnutrition status, and patients will be scored as A (well-nourished), B (moderately malnourished or suspected malnutrition), and C (severely malnourished).

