### Sample size

Based on a previous electroacupuncture study on gastric emptying function, the response rate is approximately 50–70% [26–30]; however, the data of sham electroacupuncture are insufficient. Thus, we assumed that the response rates of the TEA group and sham-TEA group were 50% and 20%, respectively. Therefore, Δ is 30%. We estimated the sample size using the following formula:
$$ n=\frac{2{\left({\mu}_{\alpha }+{\mu}_{\beta}\right)}^2P\left(1-P\right)}{\Delta ^2} $$

A sample size of 66 patients will give us a power of 90% (*β* = 0.1) with a two-sided significance level of 0.05 (*α* = 0.05). To compensate for a 20% expulsion rate, a total of 90 patients will be required for the study. We will design a ratio of 2:1 (60 patients in the TEA group, 30 patients in the sham-TEA group) based on the response rates of the two groups.

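### Multiple linear regression is prescribed for predictors of all outcome measures, although response, the endoscopic findings, dichotomised HADS and PG-SGA grade are binary or ordinal

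*Protocol article*

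**What the plan says.** The only multivariable method in the protocol article is in Statistical analysis: "Univariate and multivariate analyses with multiple linear regression will be used to identify independent predictors of outcome measures". No outcome is excepted, and no logistic or ordinal model is named anywhere.

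The outcome measures include several that are not continuous:

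- Total response rates, a primary outcome: "We will compare the total response rates between the two groups". The Sample size section rests on it: "we assumed that the response rates of the TEA group and sham-TEA group were 50% and 20%, respectively".
- Endoscopic features: "We will compare the ratios of reflux esophagitis, gastritis, and gastric stasis between the two groups".
- PG-SGA, under Nutritional status: "patients will be scored as A (well-nourished), B (moderately malnourished or suspected malnutrition), and C (severely malnourished".
- HADS, under Psychological status, read as positive when the total exceeds 10.

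Others are continuous. The remaining primary outcomes are the scintigraphic ones: "We will compare the recorded residual rates and the time to 50% residual rate between the two groups as the primary outcomes". Laboratory values and SF-36 scores are also continuous.

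The sentence just before the regression sentence deals with categorical data in unadjusted form: the chi-square "test will be used for categorical data such as the PG-SGA, HADS, and adverse events".

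**The concern.** The same paragraph calls PG-SGA and HADS categorical for the chi-square test and then sets a linear model for predictors of outcome measures without exception. The chi-square test is unadjusted and cannot identify independent predictors, so it does not fill the gap.

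Applied to a yes/no or graded outcome, linear regression has three faults:

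1. **Fitted probabilities.** Once covariates enter, nothing keeps them between 0 and 1.
2. **Scores for A/B/C.** The grade must be coded as numbers, which makes the step from A to B worth exactly the step from B to C. The protocol neither states nor defends that.
3. **Standard error.** The model assumes one variance for everyone, but the variance of a yes/no outcome is p(1 − p) and changes with the rate. With unequal arms the resulting error does not cancel.

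At stake are the intervals and fitted values in the predictor analysis of response, endoscopic findings, HADS and PG-SGA.

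**Working it through.** **Inputs from the protocol article.** Response 50% (TEA) and 20% (sham), 2:1 allocation, 90 patients randomized, 20% loss (all from Sample size). Evaluable: 90 × 0.8 = 72, or 48 TEA and 24 sham.

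**The plan's own figure.** Sample size states 66 patients before losses for 90% power at two-sided 0.05. The printed formula with P = 0.35 gives 2 × (1.960 + 1.282)² × 0.35 × 0.65 / 0.30² = 53.1, so 54 per arm and 108 in total. The 66 is therefore not reproduced. That is a separate matter; nothing below uses the 66.

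**Step 1: standard error (SE) of the arm difference for a yes/no outcome.**

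- Linear model: SE = √[s²(1/n₁ + 1/n₂)], with expected s² = [(n₁ − 1)p₁q₁ + (n₂ − 1)p₂q₂]/(n₁ + n₂ − 2) and q = 1 − p.
- True: SE = √(p₁q₁/n₁ + p₂q₂/n₂).
- For n₁ = 48 and n₂ = 24, 1/48 + 1/24 = 0.0625.

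*Response, 50% vs 20% (protocol rates).*

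- s² = (47 × 0.25 + 23 × 0.16)/70 = 15.43/70 = 0.2204.
- Linear SE = √(0.2204 × 0.0625) = 0.117.
- True SE = √(0.25/48 + 0.16/24) = √0.011875 = 0.109.
- Ratio 1.077: 7.7% too wide. Simulated coverage of the 95% interval is about 96%.

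*An adverse endoscopic finding that TEA reduces (assumed rates).* The protocol gives no endoscopic rates for its arms. For sham I take 40%, the figure for gastric stasis that the Background cites from an earlier series. The TEA rate is an assumption, so a range is shown.

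- At 20% TEA: s² = (47 × 0.16 + 23 × 0.24)/70 = 13.04/70 = 0.1863.
- Linear SE = √(0.1863 × 0.0625) = 0.108.
- True SE = √(0.16/48 + 0.24/24) = √0.01333 = 0.115.
- Ratio 0.934: about 7% too narrow, simulated coverage 93.3%.

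| TEA rate (assumed; sham 40%) | Linear SE vs true SE | Simulated coverage |
|---|---|---|
| 25% | 4% too narrow | 93.9% |
| 20% | 7% too narrow | 93.3% |
| 10% | 14% too narrow | 89.9% |

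*No treatment effect.* With p₁ = p₂ = p, s² = (47 + 23)pq/70 = pq. The linear SE then equals the true SE exactly. Simulated type I error at 48:24 was 0.050 with 20% in both arms and 0.054 with 50% in both.

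The direction follows a simple rule. The SE is too wide when the larger arm (TEA) has the larger variance, and too narrow when it has the smaller.

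**Step 2: fitted probabilities.** With arm alone, the linear model returns the two observed rates and cannot leave 0 to 1. With covariates it can. In simulated covariate-adjusted models at 60:30 (4,000 trials per setting, four assumed strengths of covariate effect), 4% to 13% of fitted response probabilities fell outside 0 to 1. At least one did so in 70% to 100% of trials. In the same runs the SE of the treatment term was 3.5% to 9.6% too wide. The documents give no covariate effects, so these figures show a range and are not a forecast.

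**Step 3: information available for response.** Expected responders: 48 × 0.50 + 24 × 0.20 = 24 + 4.8 = 28.8, about 29.

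**The case against.** The strongest reply is that the reading is not forced. Several primary and secondary outcomes are continuous and linear regression suits them. The sentence does not say outright that response or PG-SGA grade will be regressed, and a condensed article may leave the model for each outcome to a fuller document. The chi-square sentence is open-ended, so it naturally covers response and the endoscopic findings. The treatment comparison for the powered outcome therefore does not depend on linear regression.

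Much of this stands. It makes the point one about a secondary predictor analysis and not about the primary comparison. It does not remove the point, because the article fixes a method and applies it to outcome measures without exception. That is a stated choice, not an omission.

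A reader might infer that the trial's error bars are wrong in both directions as an established fact. The documents do not support that. At the protocol's own response rates the error runs one way, toward wider intervals. The too-narrow direction needs endoscopic rates that the protocol does not give. A reader might also infer that false-positive treatment claims are inflated, but when the arms do not differ the standard error is right and type I error is close to nominal.

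Nor is the lack of odds ratios a fault. A risk difference is a legitimate summary, and the Sample size section itself works with a difference of 30 points.

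**Conclusion.** The point holds for the secondary predictor analysis. The protocol prescribes linear regression for outcomes that include binary and ordinal ones, and names nothing suited to them.

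The effect on standard errors is modest: about 7.7% too wide for the arm difference in response at the protocol's rates, about 7% too narrow for an endoscopic finding at an assumed 40% vs 20%, and none when the arms do not differ. These sizes rest on 48:24 evaluable patients and on a model with arm alone.

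The out-of-range fitted probabilities, which depend on assumed covariate effects, and the equal spacing imposed on A/B/C are the stronger reasons to change the model. The unadjusted chi-square comparison of the arms is untouched.

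**What to change.** Replace the regression sentence in Statistical analysis with one that matches model to outcome:

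- linear regression for continuous outcomes only: residual rates, time to 50% residual, laboratory values and SF-36 scores;
- logistic regression for response, reflux esophagitis, gastritis, gastric stasis, and HADS above or below its cut;
- proportional-odds regression for PG-SGA grade;
- treatment arm included in each model.

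The cost is wording. No extra patients or data are needed, both added methods are standard, and the article reports recruitment as still ongoing. The small downside is that about 29 expected responders support only a few predictors for response, so the candidates should be few and chosen in advance. A penalised logistic fit for rare endoscopic findings is optional.

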##### Serum examination

The likely mechanisms of TEA are activation of somatic and peripheral nerves, anti-inflammatory effects, and functional preservation of the interstitial cells of Cajal [19]. Thus, blood will be taken for the analysis of serum norepinephrine (NE), tumor necrosis factor-α (TNF-α), interleukin-1β (IL-1β), interleukin-6 (IL-6), and glucose.

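### Continuous outcomes are to be summarised as medians but tested with t tests on means, so the reported summary and the P value describe different quantities and can disagree

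*Protocol article*

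**What the plan says.** All of the relevant text is in the Statistical analysis section of the protocol article.

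- **Summary statistic:** "The results will be aggregated as median values". No outcome is excepted.
- **Residual rates, between arms:** a Student's t "test will be performed to assess the difference in the measurements", namely the residual radioactivity at six times from 45 to 120 min. The section on gastric emptying function makes these rates a primary outcome.
- **Laboratory markers, LF/HF and QoL, within each arm:** a paired Student's t "test will be used to compare the differences in serum albumin, NE, TNF-α, IL-1β, IL-6, glucose, LF/HF (sympathovagal ratio), and QoL" between baseline and 4 weeks.
- **Categorical outcomes:** a χ² "test will be used for categorical data such as the PG-SGA, HADS, and adverse events".
- **Predictors:** "Univariate and multivariate analyses with multiple linear regression will be used to identify independent predictors of outcome measures".

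The section names no transformation, distribution check or rank-based test. The article gives no SD or distribution for any continuous outcome, and its Data Availability section says that no baseline or pilot data exist.

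**The concern.** A t test, paired or unpaired, assesses a difference in means. If the figure printed beside its P value is a median, the reader has an estimate that the test did not assess and a test whose own estimate is not the one chosen for reporting. The two coincide when distributions are symmetric and samples are large. Otherwise they can diverge, and in samples of this size they can point in opposite directions.

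The outcome most exposed is the set of residual rates, because it is primary and is the continuous between-arm comparison that the section spells out. A lesser matter concerns the concentrations (NE, TNF-α, IL-1β, IL-6) and the LF/HF ratio. If these turn out to be right-skewed, a t test on raw values is less efficient than one on logs, and a multiplicative effect is easier to read as a ratio.

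**Working it through.** The plan gives no figure on this point to reproduce. The check sets its sentences side by side and then measures how far a mean-based test and a median can part.

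**1. Scope of the mismatch**

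| Outcome | Planned test | Target of the test | Stated summary |
|---|---|---|---|
| Residual rates (primary) | Student's t, between arms | difference in means | median |
| Albumin, NE, TNF-α, IL-1β, IL-6, glucose, LF/HF, QoL | paired t, within arm | mean change | median |
| PG-SGA, HADS, adverse events | χ² | proportions | median does not apply |
| Total response rate (primary) | proportion | proportion | median does not apply |

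The mismatch covers the first two rows.

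**2. Can the two disagree without skew?** Inputs: 60 and 30 patients, less the 20% loss allowed for in the Sample size section, give 60 × 0.8 = 48 and 30 × 0.8 = 24. In simulated normal data, the observed mean and median differences had opposite signs in about 13% of trials at a true difference of 0.25 SD, and in 4% at 0.5 SD. The true differences are assumptions.

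**3. How far apart are they with skew?** For a log-normal variable with log-SD s, mean/median = exp(s²/2):

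- s = 0.3: exp(0.045) = 1.05
- s = 0.5: exp(0.125) = 1.13
- s = 0.8: exp(0.32) = 1.38
- s = 1.0: exp(0.5) = 1.65

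Take two arms with equal true medians, log-SD 0.5 in the arm of 48 and 0.8 in the arm of 24. The true means differ by a factor exp((0.64 − 0.25)/2) = 1.22, and the t test rejects in about 20% of trials. With the larger spread in the larger arm it rejects in about 5%, so the result depends on the pattern. With equal spreads it also rejects in about 5%.

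**4. Raw or log scale for the skew-prone markers.** Assumptions, none of them from the article: log-normal values, correlation 0.6 between baseline and 4 weeks, a 20% fall (ratio 0.8). The sample is n = 60, the full TEA arm. The SD of the log change is s√(2(1 − 0.6)) = 0.894s. The log-scale noncentrality is |ln 0.8| × √60 / (0.894s) = 0.223 × 7.746 / (0.894s) = 1.93/s, which is 6.4, 3.9, 2.4 and 1.9 for the four values of s. Simulated power of the paired t test, two-sided 0.05:

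| log-SD | Raw values | Log values | Loss on raw scale |
|---|---|---|---|
| 0.3 | about 100% | about 100% | none |
| 0.5 | 94% | 97% | 3 points |
| 0.8 | 49% | 67% | 18 points |
| 1.0 | 28% | 47% | 19 points |

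Repeat runs with other random seeds moved these figures by one to three points.

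A second setting used n = 48, correlation 0.5 and an effect sized for about 80% power on the log scale. It gave raw against log power of 75% and 79% at log-SD 0.3, 70% and 78% at 0.5, 60% and 78% at 0.8, and 53% and 78% at 1.0. The type I error of the raw paired test stayed between about 3% and 5% throughout, so the issue is efficiency and not validity.

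**The case against.** The strongest reply is that the sentence on medians is one loose line of description. Nothing in the article says that mean differences or confidence intervals will be withheld, and an article may leave reporting detail to a fuller plan. That stands in part: no finding should rest on the intervals not being mentioned. But the article states both the summary and the tests, and they do not match. A fuller plan would have to correct or qualify one of the two sentences, not merely add to them.

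Three stronger readings are tempting, and the article does not support them.

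- **That every result is tested with a t test.** PG-SGA, HADS and adverse events have a χ² test, and the total response rate is a proportion. The concern is confined to the continuous outcomes.
- **That choosing medians shows the sponsor expects skewed data, so power is lost.** The article says nothing about distributions. At mild skew the loss is nil or a few points. The simulated comparison also favours logs by construction, since the data were generated as log-normal with a multiplicative effect.
- **That the main result or the trial's power is undermined.** The sample size rests on response rates of 50% and 20%. The residual rates are primary, and the mismatch does touch them, but no skew has been shown for them. The markers and LF/HF are secondary and tested within arm, so power lost there does not bear on the comparison of TEA with sham.

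**Conclusion.** The concern holds for the continuous outcomes. The plan pairs a blanket median summary with tests of means for the primary residual rates and for eight secondary measures, and the two can disagree. Even with normal data, opposite signs arise in about 13% of trials at a true difference of 0.25 SD with 48 and 24 patients. That result needs no assumption of skew, only of the size of the true difference.

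The case for logs is conditional and secondary. In the fixed 20% fall setting the gain is 0, 3, 18 and 19 power points at log-SD 0.3, 0.5, 0.8 and 1.0. It rests on assumed log-normality, correlation and effect size. The t tests remain valid, and the trial's stated power is unchanged. This is a correction of wording that should be made, most of all for the residual rates.

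**What to change.** Replace the sentence on medians with text to this effect:

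- Report each t-tested outcome as the mean difference with its 95% CI: between arms for the residual rates at each time, and within arm (4 weeks minus baseline) for the outcomes given a paired test. Medians may be added as description only.
- For NE, TNF-α, IL-1β, IL-6 and LF/HF, prespecify analysis of log values with the same paired test, reported as the within-arm ratio of geometric means (4 weeks to baseline) with 95% CI.
- Summarise categorical outcomes as counts and proportions.

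Whether albumin, glucose and QoL should also be compared between arms is a separate question, and this change does not settle it.

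The cost is analysis wording. No new data or patients are needed, and the named software, SPSS, can do all of it. The change should be made before outcome data are seen by arm, so that the choice of mean, median or log scale cannot follow the results.
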